## Abstract

**Introduction:**

The aim of the QUIDS study is to develop a decision support tool for the management of women with symptoms and signs of preterm labour, based on a validated prognostic model using quantitative fetal fibronectin (fFN) concentration, in combination with clinical risk factors.

**Methods and analysis:**

The study will evaluate the Rapid fFN 10Q System (Hologic, Marlborough, Massachusetts, USA) which quantifies fFN in a vaginal swab. In QUIDS part 2, we will perform a prospective cohort study in at least eight UK consultant-led maternity units, in women with symptoms of preterm labour at 22^+0^ to 34^+6^ weeks gestation to externally validate a prognostic model developed in QUIDS part 1. The effects of quantitative fFN on anxiety will be assessed, and acceptability of the test and prognostic model will be evaluated in a subgroup of women and clinicians (n=30). The sample size is 1600 women (with estimated 96–192 events of preterm delivery within 7 days of testing). Clinicians will be informed of the qualitative fFN result (positive/negative) but be blinded to quantitative fFN result. Research midwives will collect outcome data from the maternal and neonatal clinical records. The final validated prognostic model will be presented as a mobile or web-based application.

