##### Initial fFN test

The sample taken will be run at a near bedside Hologic Rapid fFN 10Q analyser, specially adapted for the QUIDS study. As fFN (or other similar biochemical tests of preterm labour) are part of standard care, it would be unethical to blind clinicians from the qualitative fFN result. The analyser will thus reveal a qualitative fFN result (positive/negative/invalid based on a 50 ng/mL threshold) for clinicians to base clinical decision-making on, according to local protocols. The quantitative fFN result, however, will be stored as a three-letter code, blinding caregivers from the result. Samples will be run as per manufacturers instructions (described above in the section ‘health technologies being assessed’).

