##### Questionnaires

All participants who are eligible to participate will be asked to complete a STAI questionnaire before the speculum examination. The same questionnaire will be repeated on 24–48 hours postexamination. The second questionnaire will be provided on paper with a prepaid envelope to be returned by post to the Trial Office. If not returned by post, the Trial Office may try to contact the participant (with the contact details provided), to complete the questionnaire over the phone.

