##### Acceptability of fFN testing and effects on anxiety

Maternal anxiety will be measured before and after quantitative fFN testing using the validated STAI. The STAI Form Y is a widely used tool for measuring both temporary ‘state anxiety’ and the more general, long-standing ‘trait anxiety’. The STAI is designed for the self-reported assessment of the intensity of feelings of apprehension, tension, nervousness and worry. STAI-Anxiety scores increase in response to physical danger and psychological stress, making it highly appropriate for this study. The use of STAI in pregnancy studies is discussed by Hundley *et al* and we will interpret the results accordingly.^20^

The questionnaire will be administered prior to fFN testing (baseline) and 24–48 hours after the test, to assess early reactions to the test and any acute anxiety prompted by the result of the test. We will also be able to assess any differences in those presented with a high-risk or low-risk result. Although it might be interesting to assess anxiety again in the latter stages of pregnancy, it is likely that, in this population, many pregnancies will not reach full term. Thus, we believe our strategy of repeat questionnaire administration will allow measurement of longer-term anxiety induced or alleviated by the test, while minimising bias due to preterm or term delivery itself or loss to follow-up.

Follow-up interviews will be performed with a subgroup of participants (n=30) to enable deeper exploration of women’s views regarding fFN testing, to gain insight into the rationale for responses given in the questionnaires. Interviews will be conducted following confirmation of pregnancy status. Acceptability of the prognostic model will also be assessed with women and a group of clinicians. All interviews will be audio recorded with consent, and field notes taken to ensure an audit trail.

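### The anxiety objective names an exposure (quantitative fFN) and a time horizon (longer-term) that this design does not deliver; it should be restated as short-term change around a disclosed qualitative result

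*Protocol article*

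**What the plan says.** The Abstract (Methods and analysis) states the objective: "The effects of quantitative fFN on anxiety will be assessed". The same paragraph sets the disclosure rule: "Clinicians will be informed of the qualitative fFN result (positive/negative) but be blinded to quantitative fFN result".

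The section Initial fFN test gives the mechanism: "The analyser will thus reveal a qualitative fFN result (positive/negative/invalid based on a 50 ng/mL threshold" and "The quantitative fFN result, however, will be stored as a three-letter code, blinding caregivers from the result". Clinicians act on the qualitative result under local protocols.

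The section Acceptability of fFN testing and effects on anxiety describes the measurement: "Maternal anxiety will be measured before and after quantitative fFN testing using the validated STAI". On timing it says: "The questionnaire will be administered prior to fFN testing (baseline) and 24–48 hours after the test, to assess early reactions to the test". It adds that women given a high-risk result can be compared with those given a low-risk one. It considers a later measurement in pregnancy and decides against it, then concludes that the chosen strategy "will allow measurement of longer-term anxiety induced or alleviated by the test".

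Table 1, Questionnaires, and Maternal acceptability and anxiety agree on the schedule: one STAI before the speculum examination and one at 24–48 hours. The 1–6 month column of Table 1 holds only the qualitative acceptability work in 30 women.

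**The concern.** The article attributes two properties to the anxiety component that its own procedures rule out.

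- **Exposure.** A woman's anxiety can respond to information only if she receives it. Under the disclosure rule she can be told positive, negative or invalid. She cannot be told a concentration or a model-based risk by anyone looking after her. A change in STAI between the two questionnaires may reflect the qualitative result, the assessment and care around it, or the passing of the acute episode. It cannot show the effect of quantitative fFN.
- **Time horizon.** A last score at 24–48 hours measures an early reaction, as the article itself says. It carries no information on anxiety later in pregnancy.

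What is at stake is the conclusion that a reader may draw. The study's product is a decision tool built on the quantitative value. A result reported under the stated objective could be taken as evidence on how women react to the quantitative test, or on lasting anxiety, when the data hold neither.

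**Working it through.** The point turns on consistency between sections, so the check sets the statements side by side.

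| Element | What is claimed | What the procedures provide |
|---|---|---|
| Exposure | Effect of quantitative fFN (Abstract); anxiety around quantitative testing (Acceptability of fFN testing and effects on anxiety) | Positive/negative/invalid at 50 ng/mL shown; concentration coded (Abstract; Initial fFN test) |
| Time horizon | Longer-term anxiety (Acceptability of fFN testing and effects on anxiety) | STAI at baseline and 24–48 hours only (Table 1; Questionnaires; Maternal acceptability and anxiety; same Acceptability section) |
| Comparator | An effect of the test | One cohort; before/after within woman, and high-risk versus low-risk result |

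**Step 1, exposure.** The article states blinding for clinicians and caregivers. It does not say in words that women are blinded. That they do not learn the value is an inference, but a firm one: the analyser does not display the concentration, and the people who could pass it on cannot read the code. A prototype tool containing the model is shown to women and clinicians in the acceptability work (Decision support), but Table 1 attaches no STAI to that contact.

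**Step 2, time horizon.** The Acceptability section describes the 24–48 hour score as an early reaction, gives reasons for not measuring later, and then claims longer-term measurement from the same two scores. These statements cannot all hold. The STAI trait scale does not reconcile them: the article describes it as capturing general, long-standing anxiety, and it too is last taken at 24–48 hours.

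**Step 3, comparator.** No group is left untested and no group is told the concentration. Women who consent but prove ineligible for the swab at speculum examination cannot serve as controls, because they differ clinically, for example by ruptured membranes or bleeding. The within-woman change starts from an acute attendance and has nothing to be set against. The high-risk versus low-risk contrast is legitimate, but it is a contrast of qualitative results. Since clinicians act on that result, it also includes the care that follows.

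**Step 4, figures.** The only sample-size figures concern validation, and they reproduce: 1600 × 0.06 = 96 and 1600 × 0.12 = 192 events; 36 000 × 0.089 × 0.5 = 1602 recruits. No sample-size figure is given for anxiety, and none of these numbers changes.

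**The case against.** The strongest reply is that this is loose labelling. The Introduction and the section on health technologies say that fFN is now available only on the quantitative analyser, so quantitative fFN testing may simply name the device used. The Abstract states the blinding openly, close to the objective. Elsewhere the anxiety section speaks of the test result and of high- or low-risk results, which fits disclosure of the qualitative result.

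Part of this stands. The device reading is fair for the phrase about testing in the anxiety section. It does not rescue the Abstract, which promises the effects of quantitative fFN in an article that distinguishes the concentration from the single-threshold result. It does nothing for the longer-term claim.

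Four stronger readings are tempting, and the documents do not support them:

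- **That there is no comparison at all.** The high-risk versus low-risk contrast is already planned. What is missing is a comparator for the two claims as stated.
- **That the before/after change will be reported as the test effect, or used to support the tool.** The article specifies no estimator for anxiety, and the tool rests on the validated model and the acceptability work.
- **That the size of a spontaneous fall can be calculated by a regression-to-the-mean formula.** The documents give no STAI values or correlations, and women are not selected on STAI, so a formula for selection on an extreme score does not fit.
- **That telephone questionnaires fall outside the window.** The Questionnaires section says "If not returned by post, the Trial Office may try to contact the participant" and gives no timing. Late completion is plausible but not stated, and its handling may properly be left to fuller documents.

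**Conclusion.** The point holds as an inconsistency between stated claims and design. Neither the effect of quantitative fFN on anxiety nor longer-term anxiety can be answered from this cohort as described. Short-term anxiety by qualitative result can be.

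The size is limited. Anxiety lies outside the primary endpoint, the sample-size calculation and the model validation, all of which are unaffected. No number in the article is wrong on this account. The correction should be made, but it does not threaten the study's main purpose.

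The conclusion rests on one inference, that women do not learn the concentration by a route the article leaves undescribed, and on the STAI schedule being as Table 1 and the text give it.

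**What to change.** 1. Restate the objective in the Abstract and in the anxiety section as short-term (24–48 hour) change in anxiety around fFN testing with the qualitative result disclosed.
2. Make the planned high-risk versus low-risk contrast the main comparison of the 24–48 hour score, adjusted for the baseline STAI already collected.
3. Describe the overall before/after change without attributing it to the test or to quantitative fFN.
4. Delete the longer-term claim.
5. Do not restrict the main analysis to undelivered women. Delivery is the post-test event that fFN is meant to predict, so the restriction could remove women unequally from the two result groups. Report results by delivery status, or use the restriction as a sensitivity analysis.

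The cost is small: revised wording and a specified comparison using data already collected, with no new visit or questionnaire. The downside is a narrower claim, since the study would say nothing about reactions to a concentration or about anxiety beyond 48 hours.

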**Ethics and dissemination:**

The study is funded by the National Institute of Healthcare Research Health Technology Assessment (HTA 14/32/01). It has been approved by the West of Scotland Research Ethics Committee (16/WS/0068).

**Version:**

Protocol V.2, Date 1 November 2016.

**Trial registration number:**

ISRCTN41598423 and CPMS: 31277.

Strengths and limitations of this studyValidation of a prognostic model in a separate prospective cohort study.Health economic analysis to determine cost-effectiveness from National Health Service perspective.Not a randomised control trial to test effectiveness of the model on improved patient outcomes.

## Introduction

The overall aim of the QUIDS study is to develop a decision support tool for the management of women with symptoms and signs of preterm labour, based on a validated prognostic model using quantitative fetal fibronectin (fFN) testing. The study has been conceptually divided into two parts. In this, the protocol for QUIDS part 2, we detail the protocol for a prospective cohort study. This will externally validate a prognostic model developed in QUIDS part 1.^1^ More detailed background about the diagnosis of preterm labour and background to the study is provided in the introduction of QUIDS Protocol part 1.^1^

fFN is a biochemical test of preterm labour which has the potential to help improve diagnosis of impending preterm delivery.^2^ Much of the evidence about fFN to date relates to the qualitative fFN test, which provides a positive or negative result on the basis of a single threshold of 50 ng/mL.^2 3^ This test has been largely replaced with the Rapid fFN 10Q System, which provides a concentration of fFN (quantitative fFN), and as a continuous variable, may be a more useful predictor of preterm delivery. fFN is now only available with a quantitative analyser in the UK, but there is no consensus as to which women to use the test in, or how to interpret the results.

The QUIDS study will address this evidence gap by providing evidence about the potential value of the quantitative fFN test, along with guidance about how to interpret results. Here, we detail the protocol for external validation of a prognostic model developed in QUIDS part 1.^1^

## Methods and analysis

### Aims and methodologies

The aim of the QUIDS study is to develop a decision support tool for the management of women with symptoms and signs of preterm labour, based on a validated prognostic model using quantitative fFN testing.

The study protocol has been divided into two parts (see flow chart figure 1). The protocols for parts 1 and 2 are reported in separate manuscripts.

**Figure 1 F1:**
[figure not shown]
Flow chart illustrating the design of QUIDS study and conceptual division into part 1 and part 2. qfFN, quantitative fetal fibronectin.

In QUIDS Protocol part 1, we have described how we will perform (1) an individual participant data (IPD) meta-analysis and (2) and economic analysis. The protocol details how we will develop and internally validate a prognostic model using quantitative fFN (as a continuous variable) and other risk (prognostic) factors and to evaluate the added value of quantitative fFN towards this prognostic model performance. We will also provide an economic rationale for the prognostic model and analyse its cost-effectiveness from the perspective of the National Health Service (NHS).

In this, the QUIDS Protocol part 2, we will detail the prospective cohort study to externally validate and, if necessary, refine the prognostic model. This will be performed in at least eight UK hospitals with different settings (rural/urban) and different levels of neonatal care facilities. In addition, acceptability of quantitative fFN testing, and effects on maternal anxiety will be performed. We will assess the potential cost-effectiveness of the final prognostic model/decision support tool. This additional analysis will allow us to model the full costs and effect impacts of the different prognostic model and compare these in a cost-effectiveness analysis to provide an evidence-based economic rationale for implementing the diagnostic tool in the NHS.

### Endpoints

The primary endpoint of the prognostic model is spontaneous preterm delivery within 7 days of qfFN test, in women less than 36 weeks’ gestation. This was influenced by the preceding QUIDS Qualitative study, which included focus group consultation to determine the decisional needs of women, their partners and clinicians (online supplementary material). It is also a recognised clinically important endpoint, as antenatal steroids (which significantly reduce morbidity and mortality in preterm babies)^4^ are most effective if delivery occurs within 7 days of administration.

10.1136/bmjopen-2017-020795.supp1Supplementary file 1

A secondary endpoint suggested by QUIDS Qualitative study (online supplementary material) consultation, was delivery within 48 hours of qfFN test. This analysis will be performed if feasible to do so within the constraints of the data available for model development and validation.^1^

### Health technologies being assessed

The trial will evaluate the Rapid fFN 10Q System (Hologic, Marlborough, Massachusetts, USA). This provides a concentration of fFN (ng/mL or INVALID) in a vaginal swab sample in 10 min. It is now the only commercially available fFN test system, and replaces the TLiQ rapid analyser system, which provided a qualitative fFN result (POSITIVE or NEGATIVE) based on a threshold of 50 ng/mL. The Rapid fFN 10Q system is a point of care test, which clinical staff can easily perform. All reagents for fFN testing can be stored at room temperature and specimen collection kits, reagents, cassettes and the 10Q analyser can be kept in clinical areas where women with symptoms of preterm labour are assessed so they can be conveniently accessed.

Vaginal swab samples are analysed by lateral flow; solid-phase immunochromatographic assay (the Rapid fFN Cassette) and interpreted in the 10Q Rapid analyser. Two hundred microlitres of the sample is pipetted into the sample application well of the Rapid fFN Cassette using a polypropylene or polyethylene pipette. The sample will then flow from an absorbent pad across a nitrocellulose membrane via capillary action through a reaction zone containing murine monoclonal anti-fFN antibody conjugated to blue microspheres (conjugate). The conjugate, embedded in the membrane, will be mobilised by the flow of the sample. The sample will then flow through a zone containing goat polyclonal antihuman fibronectin antibody that captures the fibronectin-conjugate complexes. The remaining sample will flow through a zone containing goat polyclonal antimouse IgG antibody that captures unbound conjugate, resulting in a control line. After 10 min of reaction time, the intensities of the test line and control line are interpreted with the 10Q Rapid analyser and a printed result provided as a concentration in ng/mL (0≥500 ng/mL) or INVALID. The result is invalid if the test does not meet internal quality controls (QC) that are performed automatically with every test. In the event of an invalid result, the test can be repeated with any remaining clinical specimen. A QC can be performed by a reusable Rapid fFN 10Q QCette QC Device, which verifies that the analyser performance is within specification.

### Target population

The target population is pregnant women attending hospital with signs and symptoms of preterm labour.

### Validation and refinement of prognostic model

#### Population

The prospective cohort study will include women with signs and symptoms of preterm labour at 22^+0^ to 34^+6^ weeks gestation in whom admission, transfer or treatment is being considered. These will be recruited from at least eight sites with a mix of rural/urban settings, and have different levels of neonatal care facilities, over 12 months.

#### Eligibility criteria

The following inclusion criteria will apply at screening assessment (all apply):Women who are 22^+0^ to 34^+6^ weeks (or earlier gestation if the fetus is considered potentially viable).Women showing signs and symptoms of preterm labour which may include any or all of back pain, abdominal cramping, abdominal pain, light vaginal bleeding, vaginal pressure, uterine tightenings or contractions.Women where hospital admission, interhospital transfer or treatment (antenatal steroids, tocolysis or magnesium sulfate) are being considered due to signs of preterm labour.Women aged 16 years or above.

The broad inclusion criteria reflect current clinical practice and enable the generalisability of the results of the trial for routine clinical care. We will include women who reattend 7 days or more after initial recruitment with signs and symptoms of preterm labour and also women who remain symptomatic but undelivered 7 days later in whom repeat testing by the clinician is deemed to be appropriate. This will be in line with manufacturer’s recommendation for fFN testing.

The following inclusion criteria will apply on speculum examination:Cervical dilation ≤3 cm.Intact membranes.No significant vaginal bleeding, as judged by the clinician.Once it has been established that the women meet the above criteria, on speculum examination, the fFN swab can be taken.

Participants who sign the consent but are not eligible on examination to have an fFN swab taken will still be enrolled and have outcome data collected.

The following exclusion criteria will apply:Contraindication to vaginal examination (eg, placenta praevia).Higher order multiple pregnancy (triplets or more).Moderate or severe vaginal bleeding.Cervical dilatation greater than 3 cm.Confirmed rupture of membranes.Sexual intercourse, vaginal examination or transvaginal ultrasound in the preceding 24 hours factors may invalidate results. These women will be initially excluded from the study, but can be included if still symptomatic after 24 hours, when fFN accuracy will be restored.

#### Co-enrolment

This trial involves validating a decision support tool relating to a test that is currently commonly used in clinical practice. As such, there are no additional interventions. Co-enrolment in other non-interventional trials will be allowed. Co-enrolment in trials of tocolytic treatments or other management strategies that may influence timing of delivery as a primary outcome will not be allowed. Participation in QUIDs would not preclude babies being subsequently involved in interventional trials. Co-enrolment will be recorded in the electronic case report form (CRF).

